## Methods/design

### Study design

The study will be a nonblinded pilot RCT with two parallel groups. The protocol will follow the Declaration of Helsinki and will be conducted according to the standard protocol items: recommendations for interventional trials (SPIRIT) guidelines and the World Health Organization trial registration data set (version 1.2.1) guidelines for clinical trial protocols (see Additional file 1 and Additional file 2). It will be conducted in the Rehabilitation Department of Tongji Hospital at Huazhong University of Science and Technology in Wuhan, China. AIS subjects will be recruited from the hospital’s outpatient rehabilitation department. To recruit more subjects, we will post study-related advertisements in the Outpatient department and WeChat app. A flow diagram is shown in Fig. 1.

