### Randomization and blinding

The physician will explain the whole content of the trial to the candidates who meet the eligibility criteria in a separate room. Written informed consent from both subject and their statutory guardians are required. Their demographic information and medical history will then be recorded.

Each subject will be assigned to either the study or the control group using simple randomization with a 1:1 allocation. The random sequence will be generated by an investigator using an electronic random sequence generator (www.random.org). The numbers in the random sequence will be sealed in consecutively numbered, opaque envelopes. When required, the envelopes will be opened by a person who will not be involved in the intervention, assessment, or statistical analysis.

Due to the nature of the interventions, blinding of the therapists and subjects to the intervention type will be impossible, so only the assessors and those performing the statistical analysis be blinded to the allocation results. To ensure that the group allocation results remain concealed as much as possible, the assessors will process the assessments in a separate room, and the statistical analysis will not include the information about the subjects and their allocations. The schedule for the treatments and outcome assessments is presented in Fig. 2.

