### Assessment

Age, sex, height, weight, Risser sign, menarche status (for the girls), and type of scoliosis will be recorded at the start of the experiment. The United States Risser staging will be used to quantify skeletal maturity on a scale of 0 to 5 [43]. Stage 0 represents no ossification of the iliac apophysis, whereas stage 5 represents complete ossification and fusion. The scoliosis types will include thoracic, lumbar, thoracolumbar, and S-shaped scoliosis, corresponding to the anatomical site of the spinal deformity [1].

The primary outcome will be the feasibility of performing a full-scale study using these protocols. The time to complete enrollment, recruitment rate, subject retention, and adherence to the treatment allocation will all be important observations. The efficacy of treatment will be the secondary outcome. Spine curvature, rotation of the trunk, and postural symmetry will be assessed by the Cobb angle from X-ray images; the ATR, as measured with a Scoliometer; and 3-DPPs, as measured using a global postural system (GPS), respectively. The SEP will be assessed for evaluating sensorimotor integration, and the SRS-22 will be administered for the quality of life. The Cobb angle will be measured at baseline and at the end of 8 weeks of training. The SEP will be measured at baseline and at the end of 2 weeks of training. The ATR, 3-DPPs, and SRS-22 scores will be measured at baseline and then after 2 weeks, 4 weeks, and 8 weeks of treatment. The mean changes of Cobb angle from baseline to the end will be compared. And the mean difference of other indicators between each two visits will be used for comparative analysis.

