### Sample size

G*Power 3.1.9.7 was used to execute the power calculations. The change of the Cobb angle was chosen as the primary outcome indicator. Referring to the two studies from Zheng (*d* = 0.8) [59] and Liang et al. (*d* = 1.2) [60], we set the value of effect size *d* = 1.0 in our study. With a significance level of 5%, 17 subjects are needed in each group to reach a power of 80%. Allowing for a dropout rate of 15%, a total of 40 subjects will be recruited with 20 subjects for each.

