### Data collection, data management, and statistical analysis

The primary outcome measures will be tabulated and interpreted with respect to the goals established a priori.

To estimate the sample size required for a future full-scale RCT, between-group effect sizes and their 95% confidence intervals will be calculated by applying Hedges’ correction. A minimum power of 80% will be used to detect changes in the Cobb angles, ATRs, 3-DPPs and SRS-22 scores (*α* = 0.05). The sample size will be increased to allow for an estimated 20% dropout rate. Statistical methods for the secondary outcome measures will be evaluated via comparisons of changes between groups.

The data will be double entered into EpiData 3.1 software (The EpiData Association, Odense, Denmark) and then transferred to version 22.0 of the SPSS software suite (IBM, Armonk, NY, USA) for the analyses. The threshold for significance will be taken as *α* ≤ 0.05. A statistician who will be blinded to the allocation results will analyze all the data. The continuous variables will be presented as means ± SDs, and the categorical variables will be presented as ratios. The baseline readings will be compared using independent samples *t* tests or chi-squared tests. For the Cobb angles and SRS-22 scores, independent samples *t* tests will be used to compare the two groups, and paired *t* tests will be used for within-group comparisons. For the M, U, MU, and M+U SEP peak amplitudes and latencies, nonparametric Wilcoxon signed-ranks tests will be used to compare these values between and within the groups. For the 3-DPPs and ATR, repeated measured analysis of variance will be used for the between-groups and within-groups comparison. Furthermore, we will perform subgroup analysis by age group (age < 13 years and age ≥ 13 years) [2, 33]. To deal with the missing data, a sensitivity analysis and weighted estimating equations will be used as the primary approach [61].

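### The between-group SEP comparison is assigned the Wilcoxon signed-ranks test, a paired test, although the two arms are independent and unmatched

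*Protocol article*

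**What the plan says.** Under Data collection, data management, and statistical analysis, the protocol article gives SEP peak amplitudes and latencies one test for two different comparisons: "nonparametric Wilcoxon signed-ranks tests will be used to compare these values between and within the groups".

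The structure of the data is fixed elsewhere:

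- Study design: "The study will be a nonblinded pilot RCT with two parallel groups".
- Randomization and blinding: "Each subject will be assigned to either the study or the control group using simple randomization with a 1:1 allocation". No matching is described.
- Assessment: "The SEP will be measured at baseline and at the end of 2 weeks of training", so each subject contributes one before-and-after pair.
- Assessment, on the role of the measure: "The SEP will be assessed for evaluating sensorimotor integration".

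For the Cobb angle and SRS-22, the sentence just before the SEP one keeps the two kinds of comparison apart: "independent samples *t* tests will be used to compare the two groups, and paired *t* tests will be used for within-group comparisons". No Mann-Whitney or rank-sum test is named anywhere in the article.

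**The concern.** A signed-ranks test takes one difference per pair and ranks the absolute differences. Between two independent arms there is no rule for which study subject goes with which control subject, so the statistic is undefined until someone supplies a pairing. Statistical software will usually supply one silently, from the order of the rows.

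What is at stake is the between-arm result for sensorimotor integration. The Background builds its rationale on manipulation improving sensorimotor integration, the abstract lists it among the hypothesised benefits, and SEP is the measure assigned to it. A P value that depends on an unspecified pairing cannot be reproduced by another analyst, and the plan would not stop a pairing being chosen after the data are seen.

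This is a method that the protocol states, not a detail left to an analysis plan that is not shown.

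**Working it through.** **Inputs from the article.** Two parallel arms, simple 1:1 randomization, significance threshold 0.05; 17 per group for 80% power, 15% dropout, 40 in total; and, for the Cobb angle, "we set the value of effect size *d* = 1.0 in our study".

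**Assumptions of this check.** Normal data, 17 evaluable subjects per arm, two-sided tests. The article gives no SEP effect size, so d = 1.0 is borrowed from the Cobb calculation for illustration only.

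**1. The plan's own figure.** For a two-sided independent-samples t test the noncentrality is d·√(n/2) = 1.0 × √(17/2) = 2.92 with 32 degrees of freedom. Power is 0.807 at 17 per group and 0.781 at 16, so 17 is the smallest n. Then 17/0.85 = 20 per group, 40 in total. The stated sample size is reproduced, and the present point does not alter it.

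**2. Why pairing matters.** Let X be the control values, Y the study values and π a pairing.

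- Signed-ranks: Dᵢ = Y_π(i) − Xᵢ; W⁺ is the sum of the ranks of |Dᵢ| over Dᵢ > 0. It uses 17 differences and changes with π.
- Rank-sum: U counts the pairs (i, j) with Yⱼ > Xᵢ. It uses all 17 × 17 = 289 cross-arm comparisons and does not involve π.

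**3. Spread of P over pairings of the same data.**

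| Data set | Rank-sum P | Signed-ranks P over random pairings | Share of pairings at P ≤ 0.05 |
|---|---|---|---|
| 17 per arm, placed at the threshold | 0.050 | 0.009 to 0.145 (central 95%) | 39% |
| 17 per arm, drawn at d = 0.7 | 0.148 | 0.013 to 0.644 (full range) | 1.6% |
| 20 per arm, drawn at d = 0.7 | 0.0026 | below 0.001 to 0.040 (full range) | 100% |

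Six further data sets placed at a rank-sum P of about 0.050 gave lower limits of 0.007 to 0.013, upper limits of 0.13 to 0.17, and 30% to 53% of pairings below 0.05.

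**4. How often the conclusion is affected.** Over 100 row orders per data set, the verdict at 0.05 was not the same for every order in about 19% of data sets at d = 0, 53% at d = 0.5 and 48% at d = 1.0. With a single arbitrary pairing per data set, the verdict differed from that of the rank-sum test in about 3% of data sets at d = 0 and about 9% at d = 0.5 or 1.0.

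**5. Error rate and power with one arbitrary pairing.**

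| | Signed-ranks | Rank-sum |
|---|---|---|
| Type I error (d = 0) | 0.042 | 0.046 |
| Power (d = 1.0) | 0.75 | 0.78 |

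A second run of 20,000 data sets put the signed-ranks type I error at 0.046, and the powers at 0.755 and 0.790.

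**6. Subjects without a partner.** If arm sizes are left to simple randomization, P(17:17 of 34) = C(34,17)/2³⁴ = 0.136, and the mean size difference is 34 × 0.136 = 4.6 subjects. If instead arms of exactly 20 are reached, as the Sample size section states, and six subjects are lost at random, P(equal arms) = C(20,3)²/C(40,6) = 1,299,600/3,838,380 = 0.34, and the mean difference is about 1.7. So some 2 to 5 subjects on average would be left out, depending on which description of the allocation holds.

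**The case against.** The strongest reply is that this is a naming slip. The preceding sentence separates independent from paired t tests correctly, so the authors know the distinction, and the rank-sum test also bears Wilcoxon's name. That is plausible, and it means that dependence on row order is a consequence of literal application, not a certainty. It does not remove the point: the sentence names the paired test for both comparisons, and no other section corrects it.

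A reader might infer more than the article supports:

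- *That the P value is meaningless or the false-positive rate inflated.* If the pairing is unrelated to outcome, the test keeps its level (0.042 to 0.046 in step 5). The defect is non-uniqueness, not alpha inflation.
- *That changes from baseline are not compared.* The SEP sentence speaks of values, but the Assessment section and the same statistical section say in general terms that between-visit differences and changes between groups are compared. This part of the criticism does not stand.
- *That 39% is a typical rate of reversal.* It comes from a data set placed on the threshold. Away from it, the pairing may alter the P value without altering the verdict.
- *That a main trial decision is at risk.* The primary outcome is feasibility, the interim rule uses the Cobb angle, and SEP is not in the list of measures for the future sample size. The future primary outcome is to be picked by effect size, not by this P value.

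It is also fair to say that 17 per arm reflects dropout assumed for the Cobb angle at week 8. SEP is taken at week 2, so more subjects may be evaluable.

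**Conclusion.** Wrong as written, moderate severity. The signed-ranks test is right for baseline against week 2 within an arm and wrong for comparing two independent, unmatched arms. Taken literally, it gives a between-group P value that is not unique (roughly 0.01 to 0.15 in the threshold case), drops surplus subjects of the larger arm, and costs about 0.03 in power at d = 1.0 (0.78 − 0.75), with type I error near nominal. These sizes assume normal data and 17 evaluable subjects per arm; the distribution and effect size of SEP are not given. That the arms are unpaired needs no assumption, since it follows from the stated design. A higher severity is not supported, because SEP is a secondary outcome in a pilot and no decision stated in the article turns on this P value.

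**What to change.** Replace the SEP sentence with wording to this effect:

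> For SEP amplitudes and latencies, the change from baseline to week 2 will be compared between arms with the Mann-Whitney (Wilcoxon rank-sum) test. Within each arm, baseline and week 2 will be compared with the Wilcoxon signed-ranks test.

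This also makes explicit for SEP that changes are compared. The cost is one sentence of analysis text, with no effect on sample size, data collection or participants. It should be recorded before any between-arm SEP analysis is run.

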### Monitoring and auditing

A monitoring board, including a physician, two physiotherapists, two assessors, and a statistician, will be responsible for reviewing all the data and will be allowed to conduct an audit of the trial at any time. The monitoring board will be independent from the sponsor and have no conflicts of interest. Besides the monitoring board, the Independent Supervisory Committee (ISC) in our institution will undertake the duties of monitoring the progress of experiments and data quality. It consists of one independent chair and at least six members including clinical experts, statisticians, patient, and public involvement representatives. All the data will be securely stored on EpiData software.

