### Interim analysis

An interim analysis will be conducted by statisticians when 20 subjects complete the experiment. In our study, the primary endpoint will be analyzed via the change of Cobb angle. In order to maintain the cumulative type I error rate at the planned 0.05, the Lan-Demets spending function method [62] with the O’Brien-Fleming spending function [63] will be used. The preplanned *P* value for stopping the trial owing to efficacy will be 0.00305. Our research team will discuss the results of the interim analysis with the ISC and the monitoring board to determine whether to stop the trial early. Besides, when a serious adverse event occurs in our study, the trial will also be terminated early.

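### The research team, and a monitoring board that includes physiotherapists and assessors, may see the comparative interim result, which weakens the trial's only blinding

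*Protocol article*

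**What the plan says.** Three sections of the Protocol article bear on this.

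- **Randomization and blinding.** Therapists and subjects cannot be blinded, "so only the assessors and those performing the statistical analysis be blinded to the allocation results". Two protections are described: "the assessors will process the assessments in a separate room, and the statistical analysis will not include the information about the subjects and their allocations".
- **Monitoring and auditing.** "A monitoring board, including a physician, two physiotherapists, two assessors, and a statistician, will be responsible for reviewing all the data". The board also "will be allowed to conduct an audit of the trial at any time". On independence the text says: "The monitoring board will be independent from the sponsor and have no conflicts of interest". The same section sets up a second body, the ISC, with an independent chair and at least six members, among them clinical experts and statisticians.
- **Interim analysis.** Statisticians analyse the change in Cobb angle when 20 subjects have completed, with an efficacy stopping threshold of P = 0.00305. Then: "Our research team will discuss the results of the interim analysis with the ISC and the monitoring board to determine whether to stop the trial".

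The sections on Confidentiality and Access to data restrict who may see the final data. They say that anonymized data go to the statistician during and after the trial. Neither says who may see an interim comparison.

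**The concern.** In a trial where subjects and therapists know the treatment, the masked reading of outcomes is the main safeguard against biased measurement. Scoliometer placement, posture marker placement and the choice of end vertebrae for the Cobb angle all involve judgment. The plan shares a comparative efficacy result with the research team while subjects are still to be treated and measured. It also gives a board that includes physiotherapists and assessors access to all the data at any time. Neither rule fits well with the blinding commitment.

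The consequences could reach beyond this pilot. The outcome with the largest between-group effect size is to become the primary outcome of the full trial (Primary outcome measure), and that trial is to be sized from the pilot's effect sizes (Sample size calculation). A distortion in the judgment-based outcomes could affect both decisions.

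**Working it through.** The point depends on who may see what, and when. Arithmetic enters only in the timing.

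**1. How much of the trial remains at the interim.** The inputs are 20 completers (Interim analysis), and 17 per group analysed and 40 recruited after 15% dropout (Sample size).

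- The plan's recruitment figure reproduces: 17 / (1 − 0.15) = 20 per group, so 40 in total.
- The plan's interim threshold also reproduces. With O'Brien-Fleming-type spending, 0.025 per side (two-sided testing assumed) and information fraction t = 20/40 = 0.5, it is 4 × [1 − Φ(z(1 − 0.05/4)/√t)] = 4 × [1 − Φ(2.241/0.707)] = 0.00305. At t = 20/34 the same formula gives 0.00695, so the authors placed the look at half of 40.
- If all 40 complete, 40 − 20 = 20 subjects (50%) are outstanding. If 15% drop out, 34 − 20 = 14 of 34 (41%) are. Hence up to half.

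**2. Whether the interim result is comparative.** It is. An efficacy stopping P value on Cobb change can only come from comparing the two groups.

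**3. Who receives it.** Three parties are named: the research team, the ISC and the monitoring board. The therapists and assessors are not excluded, and the research team is not limited to a recommendation.

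**4. What the board may see and when.** It may see all the data, and it may audit at any time. Exposure through the board is therefore not confined to the period after the interim. The text does not say whether all the data includes records that reveal the arm, such as those of the target segments for spinal manipulation, which only the study group receives.

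**5. Whether the board's members are the trial's own staff.** The text does not settle this.

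- Treating staff: two exercise therapists (Physiotherapeutic scoliosis-specific exercises) and one manipulating physiotherapist (Spinal manipulative therapy), so three people against two physiotherapists on the board.
- Assessing staff: an assessor for evoked potentials and an assessor for posture, who may or may not be the same person. A therapist records trunk rotation, and no reader is named for the Cobb angle.
- The role names overlap, but the counts do not establish that the people do.

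**6. What protects the blind.** The separate room and the analysis without allocation information do not govern board review or the interim discussion. The only check is an interview after the study (Randomization procedure), which can detect a lost blind but not prevent it.

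**The case against.** The strongest reply has four parts.

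- **Freedom from conflicts of interest.** Someone who treats or measures subjects while monitoring the same trial would have a plain conflict, so the natural reading is that board members are outsiders. This has real weight, and it is why a reader who infers that the trial's own assessors sit on the board goes further than the text. But the article never says that members neither treat nor assess, and the reply does not cover the research team.
- **An aggregate result is not an allocation.** Knowing which group is ahead does not tell an assessor which arm the next subject is in. This stands. The direction of effect can bias readings for one arm only if the assessor also knows or guesses the arm. That second step is possible, because subjects are unblinded and might mention their treatment, but the document does not show that it happens.
- **Charter detail.** Closed sessions and masked reports are often left to a full protocol or a monitoring charter, and this is a condensed article. Mere silence would be no finding. Here, however, the article itself states who receives the interim results and what the board may review.
- **Trunk rotation.** If the therapist who records it is a treating therapist, that outcome is already unmasked for a reason unrelated to the board. This stands, and changing the board would not cure it.

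A reader might also want to assume a shift in the later readings and turn it into a bias or an inflated type I error. The documents give no basis for any such shift, and the calculation would require the arm of the remaining subjects to be known. No figure of that kind belongs here.

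**Conclusion.** The point holds as a weakness in stated rules, not as a demonstrated loss of blinding. The research team's access to the comparative interim result is explicit. The exposure through the board is conditional: it depends on whether its physiotherapists and assessors also work on the trial, and on whether the data they review reveal allocation. Together these rules weaken the blinding of assessors and analysts, which is the only blinding the trial has.

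In extent, the interim route touches up to 20 of 40 subjects, and the board route could touch more. The effect on the estimates cannot be quantified from the document. The point deserves correction because the safeguard matters and an alternative body already exists.

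**What to change.** **Interim analysis.** State that comparative interim results go only to the ISC, and that the research team is told only whether to continue or stop.

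**Monitoring and auditing.** State that nobody who treats or assesses trial subjects sits on the monitoring board. Alternatively, state that any such member sees only pooled, masked data until database lock. If the board's members are already separate from trial staff, one sentence saying so settles that part.

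**Cost.** This is a change of protocol wording. It uses the existing ISC, which already includes statisticians and clinical experts, and needs no extra staff. The downside is that the research team sees less before the end of the trial.
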